## Abstract

**Background:**

Cognitive impairments are a key aspect of schizophrenia spectrum disorders (SSDs), significantly affecting clinical and functional outcomes. The COVID-19 pandemic has heightened concerns about mental health services and cognitive stimulation opportunities. Despite evidence-based interventions like action-based cognitive remediation (ABCR) and metacognitive training (MCT), a research-to-practice gap exists in their application across mental health settings.

**Objective:**

The iCogCA study aims to address this gap by implementing digital ABCR and MCT through a national Canadian collaborative effort using digital psychological interventions to enhance cognitive health in SSDs.

**Methods:**

The study involves 5 Canadian sites, with mental health care practitioners trained digitally through the E-Cog platform, which was developed by our research group. Over 2.5 years, participants with SSDs will undergo pre- and postintervention assessments for clinical symptoms, cognition, and functioning. Each site will run groups annually for both ABCR and MCT, totaling ~390 participants. A nonrandomized concurrent controlled design will assess effectiveness design, in which one intervention (eg, ABCR) acts as the active control for the other (eg, MCT) and vice versa, comparing cognitive and clinical outcomes between the interventions using generalized linear mixed effect modeling. Implementation strategy evaluation will consider the digital platform’s efficacy for mental health care practitioners’ training, contextual factors influencing implementation, and sustainability, using descriptive statistics for quantitative data and thematic analysis for qualitative data.

**Results:**

A pilot pragmatic trial has been conducted previously at the Montreal site, evaluating 3 early implementation outcomes: acceptability, feasibility, and engagement. Patient and therapist acceptability was deemed as high and feasible (21/28, 75% of recruited service users completed therapy, rated feasible by therapists). Technology did not appear to significantly impede program participation. Therapist-rated levels of engagement were also satisfactory. In the ongoing study, recruitment is underway (114 participants recruited as of winter 2024), and intervention groups have been conducted at all sites, with therapists receiving training via the E-Cog learning platform (32 enrolled as of winter 2024).

**Conclusions:**

At least 3 significant innovations will stem from this project. First, this national effort represents a catalyst for the use of digital technologies to increase the adoption of evidence-based interventions and will provide important results on the effectiveness of digitally delivered ABCR and MCT. Second, the results of the implementation component of this study will generate the expertise needed to inform the implementation of similar initiatives. Third, the proposed study will introduce and validate our platform to train and supervise mental health care practitioners to deliver these interventions, which will then be made accessible to the broader mental health community.

**Trial Registration:**

ClinicalTrials.gov NCT05661448; https://clinicaltrials.gov/study/NCT05661448

**International Registered Report Identifier (IRRID):**

DERR1-10.2196/63269

## Introduction

### Background

Schizophrenia and related psychoses present debilitating challenges, imposing an enormous burden on individuals, families, and communities [1,2] and are characterized by symptom recurrence, social deterioration, and cognitive impairments [3-8]. Most affected individuals experience persistent positive (eg, hallucinations and delusions) and negative symptoms (eg, amotivation, avolition, and reduced expressivity), alongside notable cognitive challenges like difficulties in verbal memory, executive functions, and attention. In addition to these impairments are cognitive distortions [9], affecting reasoning and information processing and, collectively, represent a core feature of schizophrenia, impacting clinical and functional recovery [10-13]. Thus, addressing overall cognitive health in schizophrenia is crucial. Over the past 25 years, advancements in psychological interventions, including cognitive remediation (CR) and metacognitive training (MCT), have shown promise for the treatment of schizophrenia spectrum disorders (SSDs). Both CR and MCT have been found to enhance cognitive functioning and decrease cognitive biases [14,15].

### Cognitive Health Interventions in Schizophrenia: State of the Evidence and Delivery Format

Meta-analyses affirm the effectiveness of CR in enhancing cognition [14,16,17] and MCT in addressing cognitive biases [15,18]. Notably, various mental health practitioners with an understanding of cognitive processes can be trained to provide these interventions, providing flexibility in service delivery [19-21]. Delivered in a group format, these interventions enable practitioners to reach multiple service users simultaneously [20]. Research indicates the feasibility of using technology for remote cognitive assessment and psychological interventions, as individuals with psychosis express interest and willingness to engage with digital mental health services [22-24] and find this mode of communication more satisfying and less challenging than observed in the general population [25].

### Preliminary Work on Remote Delivery of Cognitive Health Interventions

Our preliminary work investigated the remote delivery of action-based cognitive remediation (ABCR) and MCT [26]. ABCR is a distinct form of CR, which integrates the traditional cognitive training techniques of CR with simulated workplace scenarios and goal setting [27]. This work involved evaluating 3 crucial early implementation outcomes: acceptability, appropriateness, and feasibility for both patients and therapists. Across 6 cohorts (3 ABCR and 3 MCT) conducted within Montreal, patients expressed high acceptability, with overall satisfaction for expectations and perception of progress. The interventions demonstrated feasibility; 36 participants completed therapy, attending an average of 10 MCT sessions and 12 ABCR sessions.

Using recently developed measures [28], therapists also reported excellent acceptability, appropriateness, and feasibility of the interventions [26]. Several facilitators and barriers to delivering these digital interventions were also identified. Barriers comprised patients’ clinical status (eg, more severe symptomatology and medication side effects), interaction issues (eg, lack of involvement and decreased accountability), technological challenges (eg, access to devices and the internet), program elements (eg, language options), and scheduling conflicts. On the other hand, facilitators included patients’ motivation to learn, therapist characteristics (eg, warmth and proper training), financial support for internet connectivity, program support (eg, education on interventions and ice breakers), and logistical adjustments (eg, offering evening sessions and forming smaller groups).

### Objectives

Having established the acceptability, appropriateness, and feasibility of our digital interventions that collectively represent the early stages of implementation, the next step is to examine how the proposed digital strategies promote the uptake of these interventions across mental health care settings. A major challenge with evidence-based psychosocial interventions is that very few are subsequently tested in effectiveness or implementation trials and thus have little impact on population health [29]. The field of implementation science has emerged over the last 20 years, promoting strategies to adopt and integrate evidence-based interventions and change practice patterns within specific settings. Implementation frameworks, such as the Consolidated Framework for Implementation Research (CFIR) [30], provide the roadmap and tools to achieve this. To test this implementation strategy, we propose a study spanning 5 different mental health care sites across Canada. In collaboration with partners and knowledge users, we will conduct a hybrid effectiveness-implementation trial and create a bilingual digital learning platform (English and French) to ensure the long-term use of these digital interventions nationwide. The first objective of this study is to investigate the clinical effectiveness of the digital modality of ABCR and MCT. The second objective of the study is to investigate the implementation strategy involving (1) the contextual factors influencing the digital delivery of cognitive health interventions [31], (2) the effectiveness of a digital learning platform (E-Cog) to train mental health practitioners, and (3) the sustainability of the maintenance of these interventions within current clinical settings.

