**2. Implementation (quantitative and qualitative)**					
	Evaluation of E-Cog platform: Number of practitioners invited to participate in the E-Cog training Number of practitioners agreeing to participate in E-Cog training Reasons for nonparticipation or participation Number of practitioners not agreeing to participate in E-Cog training Total number of attendees participating in all of the training modules Total number of attendees per session or module Semistructured interview (health care practitioners)	Preintervention During intervention		Health care practitioners and service users	
	Evaluation of factors influencing the implementation of the 2 digital interventions: E-Therapy Attitudes and Process Questionnaire—Therapist Version [62] Semistructured interview (service users and health care practitioners)	Postintervention (8-12 and 24-30 months after the 2 interventions are implemented)		Health care practitioners and service users	
	Sustainability: Program Sustainability Assessment Tool [63] Monitoring of the intervention offer after an effectiveness trial at each site	Postintervention		Health care practitioners and service users	

^a^CANTAB: Cambridge Neuropsychological Test Automated Battery.

^b^Denotes primary outcomes in the study.

^c^MMI: MUSIC Model of Academic Motivation Inventory.

^d^STQ: Satisfaction Therapy Questionnaire.

^e^ABCR: action-based cognitive remediation.

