To improve adherence, participants will be contacted prior to each session with reminders. If participants miss several sessions in a row, therapists or a research assistant will contact them to confirm their interest in continuing the intervention and discuss any barriers to their participation. If any adverse reactions occur during the trial, participant involvement in our study may be discontinued after a discussion with the research team. Finally, to improve and track treatment adherence, sessions will be audio recorded, and 2 sessions from each of the ABCR and MCT groups will be randomly selected for review by 2 experienced facilitators using the treatment integrity assessment tool.

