### Training Platform

E-Cog training platform [66] is a digital platform providing training certifications for ABCR and MCT interventions developed by our group following the analyze, design, develop, implement, and evaluate model for the design of digital learning platforms [67]. Each training certification includes three training modules: (1) impact of cognitive impairments in psychosis and an introduction to remediation strategies (2 hours), (2) technological tools for digital mental health (1 hour), and (3) theoretical foundations and practical delivery of ABCR (~9 hours) or MCT (~12 hours). After obtaining the training certification, mental health practitioners participate in weekly supervision by a dedicated experienced trainer using a secure videoconferencing software. Screenshots from the training platform can be found in the multimedia appendices (Multimedia Appendices 2-4).

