### Principal Findings and Comparison to Prior Work

The objectives of this study are 2-fold, focusing on both service users and mental health care providers. The first objective aims to assess the effectiveness of digital cognitive health interventions in enhancing accessibility and engagement for individuals with SSD. If proven effective, these interventions may provide an evidence-based framework for other service providers providing care for individuals with psychotic disorders and could be adapted for other populations receiving mental health services where these interventions show similar efficacy (eg, mood disorders) [78,79]. Objective 2 aims to identify facilitators and barriers to digital delivery and a digital training platform for clinicians. We anticipate that this study will introduce and validate our platform to train and supervise mental health care practitioners to deliver these interventions, which will then be made accessible to the broader mental health community. Further, these findings will furnish crucial information for the implementation of digital health technologies to improve access to psychosocial therapies for optimized care. These findings will be used to guide the implementation of similar projects across Canada. Notably, New York State has already fully integrated CR into its psychiatric care systems [80], and parallel efforts are underway in Australia [81] and the United Kingdom [82]. Collaborating with a National Steering and Implementation Committee, we will test our set of tools based on the CFIR and make them accessible to the mental health community. Site-specific implementation committees, which include patient partners, will assist with the local implementation of our cognitive health interventions.

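### The E-Cog training objective claims effectiveness and validation, but its listed measures capture only uptake and interview views; the integrity ratings already planned are not linked to it

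*Protocol article*

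**What the plan says.** The Objectives section of the protocol article splits the second objective into three parts. The second part is "the effectiveness of a digital learning platform (E-Cog) to train mental health practitioners". The abstract's Methods paragraph uses a similarly strong word: "Implementation strategy evaluation will consider the digital platform’s efficacy for mental health care practitioners’ training". The Discussion (Principal Findings and Comparison to Prior Work) states the expected conclusion: "We anticipate that this study will introduce and validate our platform to train and supervise mental health care practitioners". The platform is then to be offered to the wider field.

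Table 1, under Implementation, has a row for the evaluation of the E-Cog platform. Its quantitative entries run from "Number of practitioners invited to participate in the E-Cog training" through the numbers agreeing and declining, with reasons, to "Total number of attendees participating in all of the training modules" and attendance at each module. A practitioner interview is the remaining entry. The Data Analysis section assigns descriptive statistics and thematic analysis to all implementation objectives.

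Elsewhere, under Cognitive Health Interventions, sessions are audio recorded, and two sessions from each of the ABCR and MCT groups "will be randomly selected for review by 2 experienced facilitators using the treatment integrity assessment tool". The purpose given there is treatment adherence. Strengths and Limitations mentions fidelity checks again, as a way to handle differences between sites. The Training Platform section adds that after certification "mental health practitioners participate in weekly supervision by a dedicated experienced trainer".

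**The concern.** An objective about how well a platform trains people needs at least one measure of what the trained people can do. The E-Cog row has none: no knowledge test, skill or competence rating, fidelity score or before-and-after measure. Full attendance followed by poor delivery, and patchy attendance followed by good delivery, would be ranked the wrong way round by the outcomes listed for this objective.

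At stake is the conclusion drawn from the implementation arm. If the plan is followed as written, E-Cog could be reported as effective and validated on completion and favourable interviews, and then released nationally on that basis. Observed delivery would not enter the judgement, even though the trial rates it.

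**Working it through.** No sample size, power or error rate is involved, so the check sets the objective against its measures.

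**Step 1. Match each E-Cog entry in Table 1 to what it can show.**

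| Entry in the E-Cog row | What it shows | Delivery quality? |
|---|---|---|
| Invited, agreeing, declining | Reach and acceptance | No |
| Reasons for taking part or not | Barriers and motives | No |
| Attendance at all modules, and per module | Completion | No |
| Practitioner interview | Self-reported experience | Not as observed performance |

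The therapist questionnaire on attitudes and process in electronic therapy sits in a different row, on factors influencing implementation. By its name it is not a skill measure either.

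**Step 2. See whether the analysis text fills the gap.** The Data Analysis section gives descriptive statistics, thematic analysis and a side-by-side comparison of the two. It adds no competence criterion and does not mention the integrity ratings.

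**Step 3. See what the current figure can support.** The Results section gives 32 therapists enrolled and 25 who have completed training.

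- p = 25/32 = 0.781.
- Wilson 95% interval with z = 1.96: centre = (p + z²/2n)/(1 + z²/n) = (0.7813 + 0.0600)/1.1200 = 0.751. Half-width = z·√(p(1−p)/n + z²/4n²)/(1 + z²/n) = 1.96 × 0.0792/1.1200 = 0.139. The interval is 61% to 89%.

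This is a snapshot of completion while training is ongoing. A narrower interval would still describe completion.

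**Step 4. See which existing data bear on delivery.** The integrity ratings do. How many there will be cannot be fixed from the article. If the rule is two sessions per cohort, the number depends on cohort size, which must be assumed:

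- 28 pilot attendees over 6 cohorts (Results): 28/6 = 4.67 per cohort; 390/4.67 ≈ 84 cohorts; 84 × 2 = 168 rated sessions.
- 36 pilot completers over 6 cohorts (Preliminary Work): 36/6 = 6 per cohort; 390/6 = 65 cohorts; 65 × 2 = 130 rated sessions.

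The sampling sentence could also mean two sessions per intervention, which would give far fewer. The planned number of practitioners is 4 to 6 at each of 5 sites, so 20 to 30. Because sampling is by group, some practitioners might have no rated session. The point depends on none of these counts.

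**Step 5. See what the ratings could and could not establish.** They could describe the integrity with which E-Cog-trained, supervised practitioners deliver. They could not attribute it to E-Cog: there is no other form of training to compare with, no rating before training, and supervision follows certification for everyone.

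**The case against.** The best defence has four parts.

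- *The article is a condensation.* Table 1 is a summary, and the full protocol may describe a certification test or say where integrity ratings are reported. That is possible, and the absence of such detail would not by itself be a finding. But here the objective and its measures are both stated, the measures down to separate attendance counts, and they do not match.
- *The aim is uptake.* The Objectives section introduces the work as examining how digital strategies promote uptake, and the counts measure that directly. This is fair, and it is a reason to keep the counts. It does not justify the stronger words used for part 2 of the objective.
- *The trial can detect poor delivery.* This stands. A reader might infer that no planned data could reveal poor delivery, or that the ratings serve adherence alone. Neither is right: the ratings are planned, and the limitations paragraph also uses fidelity checks for site consistency. The gap is that they are not tied to E-Cog.
- *Supervision belongs to the package.* This also stands. The Discussion speaks of a platform to train and supervise, so supervision should not be treated as contamination. It should be named in the claim.

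A reader might go further and infer that using the integrity ratings would show that E-Cog produces competent practitioners. The documents do not support that, for the reasons in the last step of the working. Nor do they say whether the tool scores competence as well as adherence, or has an adequacy level.

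**Conclusion.** The point holds as a mismatch between a stated objective and its stated measures. The E-Cog row supports conclusions about uptake and practitioners' views. It does not support effectiveness, efficacy or validation. The trial already plans ratings that would support a more useful, though still descriptive, statement, and does not assign them to this objective.

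The weight is moderate. One named implementation objective cannot be answered by the measures listed for it; the primary clinical outcomes and their analysis are untouched. No numerical size attaches to it beyond the 78% completion figure, which carries no information on delivery. The conclusion assumes that no skill or integrity measure is assigned to E-Cog in a full protocol not shown here. If one is, the article needs only to say so.

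**What to change.** 1. In Table 1 and the Data Analysis section, list the existing integrity ratings as a quantitative outcome for part 2 of the second objective. Link each rating to the practitioner or practitioners who delivered the session. Summarise descriptively by intervention and site, against a prespecified adequacy level if the tool has one.
2. Label the invitation, acceptance and attendance counts as uptake, and keep the interview as it is.
3. Where E-Cog is concerned, replace the words effectiveness, efficacy and validate in the abstract, Objectives and Discussion with *uptake of, and delivery integrity after, E-Cog training with weekly supervision*.
4. Optionally, draw one of the two reviewed sessions from early in a practitioner's first group, when supervision has had least time to act. All sites had already run cohorts, so this is feasible only for groups still to come or for which recordings exist. That session would no longer be a simple random pick.

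The cost is wording, some work to link ratings to practitioners, and a more modest headline claim. The descriptive summary uses ratings already planned. Because sampling is by group, it may not cover every practitioner, so coverage should be reported. A proportion calculated over all certified practitioners could need additional ratings.

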## Methods

### Study Design

A hybrid effectiveness-implementation trial [32-34] relying on digital technology will be used. The effectiveness component involves assessing the outcomes of these interventions, while the implementation component focuses on conducting the research in a way that emulates the naturalistic clinical setting. This design is ideal for transferring evidence-based behavioral interventions into real care environments [32-35], as it confirms clinical effectiveness while targeting necessary procedures to deliver and sustain such interventions in real-world care settings. A nonrandomized concurrent controlled design will be used to assess clinical effectiveness where one intervention acts as the active control for the other. The nonrandomized concurrent controlled design was selected, as it eases access to the preferred intervention by service users, overcoming the challenges of randomizing participants in real care settings and facilitating recruitment.

### Study Setting

This study takes place across 5 sites providing care to those with psychotic disorders across Canada. These sites include the Centre intégré universitaire de santé et de services sociaux (CIUSSS) de l’Ouest-de l’Ile de Montréal, Royal Ottawa Health Care Group, Kingston Health Sciences Centre, Ontario Shores Centre for Mental Health Sciences in Toronto, and Vancouver Coastal Health. We will recruit 390 service users across the 5 sites.

